### Secondary endpoints

Secondary endpoints include each element of the composite primary endpoint to investigate dose-related toxicities, as well as serum DON levels used to calculate PK parameters of the drug. Additional secondary endpoints for all participants include PK parameters such as volume of distribution, maximum concentration (*C*_max_), time to maximum concentration (*T*_max_), area under the curve (AUC), clearance, elimination rate constant, and terminal half-life (*T*_½_). Non-compartmental analysis is used for the estimation of PK parameters.

### Exploratory endpoints

Exploratory endpoints in the pediatric cohort measure efficacy.Brain volume score on MRI at admission and 24 h post-randomization, if MRI is availableNumber of minutes of electrographic seizures within the first 12 h after DON administration, as measured by cEEG monitoringEEG amplitude, frequency, and power analysis for samples collected pre-DON and at 3, 6, and 12 h post-DON administrationCerebrospinal fluid (CSF) sampled before and 4 h after DON administration analyzed for a variety of parameters including, but not limited to, changes in metabolic profiles and immune markersTCD phenotype and flow velocities measured before and 4 and 24 h after DON administration

### Participant timeline {13}

In adults, after the consent document is reviewed and signed by adult participants and eligibility is confirmed, participants remain in the research clinic for 24 h (Fig. 1A). Blood samples are drawn for pre-DON PK and baseline safety studies. Adults with uncomplicated malaria receive IV normal saline at a rate of 125 mL/h (maintenance). Oral antimalarials are administered in those with uncomplicated malaria. Each participant receives ondansetron (8 mg) 30 min before DON and 6 h after DON administration. Participants receive DON IV, at the pre–specified dose. Blood is drawn before and at 10 min, 30 min, 60 min, 90 min, and 3 h, 6 h, 12 h, and 18 h post-DON to calculate PK parameters. Twelve and 24 h, and again 7 and 14 days after DON administration, blood samples for safety are obtained. Adults have telephone or in-person safety interviews 3 months after receiving DON. Six months after receiving DON, adult participants return for a safety interview and physical examination.

Similarly, pediatric participants who fulfill enrollment criteria have pre-DON laboratory studies for safety and DON levels (Fig. 1B). Next, an IV line is placed, and participants receive IV fluids at standard maintenance rates. At enrollment, a lumbar puncture (LP) is performed both to rule out bacterial CNS co-infection and for DON mechanistic studies. IV artesunate is administered immediately upon confirmation of a CM diagnosis. Participants undergo a brain MRI (if available), TCD, and at least 30 min of EEG recording before administration of DON (or placebo). Participants remain hospitalized for a minimum of 24 h. Each pediatric participant is pre-medicated with ondansetron (0.15 mg/kg up to 5.0 mg) and receives DON IV or placebo at the pre-specified dose 30 min later. Ondansetron dosing is repeated at 8 and 16 h after DON administration. Due to the precariousness of CM and the young age of the pediatric participants, PK studies are employed through sparse sampling techniques at three of the following time points: 10 min, 30 min, 60 min, 90 min, and 3 h, 6 h, 12 h, and 18 h post-DON. A population PK analysis is used to estimate PK parameters in children. A repeat LP is performed 4 h after DON or placebo administration for metabolic studies. Participants remain hospitalized until their BCS is ≥ 3, they can drink unaided, and can sit with minimum assistance. Seven and 14 days after DON administration, blood samples for safety are obtained. At 1 and 6 months post-admission, surviving pediatric participants are examined for neurological sequelae and assigned a Glasgow Outcome Score (GOS-E) category.

Should any AEs or SAEs occur, they will be followed until resolution. During the 6-month enrollment period, should participants develop any clinical symptoms of concern, they are encouraged to return to visit study personnel for evaluation.

### Sample size {14}

A sample size of 72 pediatric participants was chosen for logistical and feasibility reasons and is based on previous experience, both with respect to historical case numbers and ward infrastructure, with enrollments in similar phase I studies at the study site. We calculated the power to show certain effects with this sample size. The calculations for power to detect safety signals are from participants who received DON in the first 2 cohorts (*N* = 14), the first 3 cohorts (*N* = 28), and the first 4 cohorts (*N* = 56). The calculations for the exploratory efficacy endpoints use sample sizes of *N* = 36 (8 placebo vs. 28 DON) for the first half (cohorts 1, 2, and 3), and *N* = 72 (16 placebo vs. 56 DON) total enrollment. From those calculations, we see that the assumed effect sizes needed to have sufficient study power to ascertain differences between dosing groups are not unreasonably large. Most outcomes are measured within 7 days of enrollment during hospitalization. Adherence with 6-month follow-up visits was 85% in previous studies. Thus, we expect a very low attrition rate of up to 15% at the 6 months post-randomization visit. The goal of the pediatric study is to assess safety and explore a dose–response association for any safety or preliminary efficacy outcomes. We did not power the study to detect small effect sizes in any of the exploratory efficacy endpoints evaluated in the pediatric participants. Nevertheless, there is sufficient sample size to detect large effect sizes in continuous exploratory endpoints between two doses and placebo for a preliminary benefit-risk assessment before the fourth cohort of pediatric enrollments or for the final analysis.

For dichotomous (i.e., present/absent) safety endpoints, we calculate exact 90% central confidence intervals for the rate per participant, so that we are 95% confident that the rate is less than the upper limit. If the true rate for participants receiving DON is equal to an anticipated SAE background rate of 20%, then with a sample size of 14 participants receiving DON, we have over 85% power to show with 95% confidence that the true rate is not greater than 54%. Repeating those same calculations with sample sizes of 28 (and 56), we have over 85% power to show with 95% confidence that the rate is not greater than 46% (37%).

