## Introduction

### Background and rationale {6a}

Cerebral malaria (CM), defined as an otherwise unexplained coma in someone with *Plasmodium falciparum (Pf)* parasitemia, is the most lethal form of severe malaria [1, 2]. Ninety percent of CM mortality occurs in children, the vast majority of whom are less than 5 years old [3]. Despite treatment with the highly effective anti-malarial, intravenous (IV) artesunate, mortality rates are 15–25%, and children who survive often suffer severe neurological sequalae. At present, there are no predictive diagnostics for which children with malaria will develop CM nor therapy for CM after children progress to severe disease. Thus, the public health burden is enormous.

Current knowledge of the cellular and molecular mechanisms that underlie CM disease pathology are incomplete. The observation of heavily infected red blood cell (iRBC) sequestration in the cerebral vasculature of children who died of CM, often accompanied by intra- and peri-vascular pathology including ring hemorrhages, led to the generally accepted hypothesis that iRBC sequestration in the cerebral vasculature and the resulting mechanical obstruction lead to inflammation, impaired vasoregulation, and blood brain barrier (BBB) dysfunction thus causing this severe progression of malaria [4]. Therapies targeting the purposed downstream effects of sequestration were investigated in multiple clinical trials [5–19], but none improved clinical outcomes. These failures suggested that the downstream effects of iRBC sequestration were poor targets of therapies.

Studies in the mouse model of CM (referred to as experimental cerebral malaria or ECM) provided strong evidence for the role of parasite specific CD8^+^ T cells in the pathology of CM [20]. CD8^+^ T cells had not been targeted for CM therapy in humans, in part, because they had not been reported in the cerebral vasculature of children who died of CM [21, 22]. We recently provided definitive evidence for the presence of CD8^+^ T cells lining the cerebral vasculature in children who died from CM [23]. Our findings point to a mechanism by which CD8^+^ T cells function in disease pathophysiology based on the extraordinary similarities in the distribution of CD8^+^ T cells in the brains of children with CM and in mice with ECM. These observations open new avenues for treatment of CM that involve modulating CD8^+^ T cells with the wealth of available T cell targeting therapeutics.

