#### Pediatric halting rules

The pediatric study pauses enrollment if the number of participants with SAEs in any single MedDRA group exceeds rates expected in children with CM. The expected rates were derived from calculating the cumulative probability of stopping when the true rate of the proportion of participants in a specific MedDRA classification group is a given percent (i.e., 25, 30, 40 or 50%). For example, 9 participants out of the first 17 enrolled must have an SAE within a single MedDRA classification group for the study to pause for review. (This will indicate a single important toxicity that should be considered before further enrollments.) A halt is not triggered, however, if of the first 17 enrolled pediatric participants, 9 experience SAEs in different MedDRA classification groups (e.g., 3 participants die, 3 participants have renal failure, and 3 participants have severe thrombocytopenia). High rates of both adverse outcomes and abnormal laboratory values are expected in pediatric CM. Therefore, only single recurring SAEs within a MedDRA classification group will initiate a pause for safety review. The properties for the halting rules were estimated by Monte Carlo simulation with 100,000 replicates. At any halt, the DSMB will review the data and evaluate whether the study should stop due to safety concerns.

Although we will only report SAEs to the regulatory bodies that have a reasonable possibility of being related to the intervention, for the purpose of applying halting rules, all events (deaths, disability, etc.), even if not specifically reported as SAEs related to treatment, will be documented.

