### Primary endpoints

In adult participants, the primary endpoint is any grade 2 or 3 AE or SAE in the 14 days after DON administration. In pediatric participants with CM, the primary endpoint includes any SAEs at any time within 14 days after DON administration. The list of solicited AEs is based on known AEs from previous DON trials. All other AEs are documented as unsolicited events. AE grading (Tables 2 and 3) was adapted from the National Institute of Allergy and Immunology (NIAID) Division of AIDS (DAIDS) toxicity tables criteria [43].

**Table 2 Tab2:** Toxicity grading scales for adult participants

Parameter	Grade 1	Grade 2	Grade 3
White blood cells (10^3^/μL)	2.0 to 2.39 if normal baseline 35% reduction from baseline, if abnormal baseline	1.5 to 1.99 if normal baseline 50% reduction from baseline, if abnormal baseline	Less than 1.5 if normal baseline 65% reduction from baseline, if abnormal baseline
Hemoglobin (g/dL)			
Healthy male Normal baseline	10 to 10.9	9 to < 10	< 9
Healthy female Normal baseline	9.5 to 10.4	8.5 to < 9.5	< 8.5
Uncomplicated malaria^a^	35% reduction from baseline	50% reduction from baseline	65% reduction from baseline
Platelets (10^3^/μL)	100 to 116 if normal baseline 35% reduction from baseline, if abnormal baseline	50 to 99 if normal baseline 50% reduction from baseline, if abnormal baseline	< 50 if normal baseline65% reduction from baseline, if abnormal baseline
Serum creatinine	1.1–1.3 × ULN	> 1.3 to 1.8 × ULN	> 1.8 × ULN
Serum SGOT	1.25 to < 2.5 × ULN if normal baseline	2.5 to < 5.0 × ULN if normal baseline	≥ 5.0 × ULN if normal baseline
	35% increase from baseline, if abnormal baseline	50% increase from baseline, if abnormal baseline	65% increase from baseline, if abnormal baseline
Diarrhea	3 or more loose stools in 24 h, treated with dietary changes	6 or more loose stools in 24 h requiring IV rehydration for clinical stabilization, resolving within 36 h	≥ 6 loose stools in 24 h requiring IV rehydration for clinical stabilization, not resolving within 36 h
Gastrointestinal bleeding	Coffee ground emesis or positive stool hemoccult or frank bleeding with < 10% decrease in hematocrit/PCV	Coffee ground emesis or positive stool hemoccult or frank bleeding with a ≥ 10% decrease in hematocrit/PCV not requiring transfusion	Coffee ground emesis or positive stool hemoccult or frank bleeding with a ≥ 10% decrease in hematocrit/ PCV requiring transfusion

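### The safety power claim of over 85% rests on a 20% SAE rate that is the mid-range of mortality alone, so it is an optimistic input for the any-SAE primary endpoint

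*Protocol article*

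**What the plan says.** The Sample size section of the protocol article sets out the method for dichotomous safety endpoints: "we calculate exact 90% central confidence intervals for the rate per participant", so that the upper limit carries one-sided 95% confidence. The planning assumption follows: "If the true rate for participants receiving DON is equal to an anticipated SAE background rate of 20" percent. For 14 children on DON the result is: "we have over 85% power to show with 95% confidence that the true rate is not greater than 54" percent. The same power is claimed for bounds of 46% with 28 children and 37% with 56. No other background rate is considered, and the article gives no basis for the 20%.

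Three other places bear on that rate:

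- Primary endpoints, for children with CM: "the primary endpoint includes any SAEs at any time within 14 days after DON administration".
- Background and rationale, on CM treated with IV artesunate: "mortality rates are 15–25%, and children who survive often suffer severe neurological sequalae".
- Pediatric halting rules: "High rates of both adverse outcomes and abnormal laboratory values are expected in pediatric CM". The same section uses death, renal failure and severe thrombocytopenia as its examples of SAEs.

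**The concern.** Death is one component of the any-SAE endpoint, so the any-SAE rate cannot be lower than the death rate over the same period. The planning rate sits at the midpoint of the article's own range for death alone. If mortality is 20%, the assumption holds only if no survivor has an SAE. The article elsewhere expects frequent adverse outcomes, names serious non-fatal events and notes severe sequelae in survivors.

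The stated power is sensitive to this rate, because each bound corresponds to a fixed maximum number of affected children. If the background rate is higher than planned, a DON group with no added risk would miss the stated bounds more often than the article implies. A monitoring board or ethics reader would then be measuring the results against a benchmark that was too favourable from the start.

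**Working it through.** **Inputs.** DON group sizes of 14, 28 and 56, the exact 90% central interval, the 20% rate and the bounds of 54%, 46% and 37% all come from the Sample size section. Mortality of 15–25% comes from Background and rationale. Any-SAE rates of 30% and 40% are assumptions made here, because the article gives no any-SAE rate other than the 20%.

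**Step 1. Reproduce the stated figures.** With x affected children among n, the exact one-sided 95% upper limit is the 0.95 quantile of Beta(x + 1, n − x). Let c be the largest x whose limit meets the stated bound. Power is P(X ≤ c) with X ~ Binomial(n, p).

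| n | c | Upper limit at c | Upper limit at c + 1 | Power at p = 20% |
|---|---|---|---|---|
| 14 | 4 | 54.0% | 61.0% | 87.0% |
| 28 | 8 | 45.7% | 49.4% | 91.0% |
| 56 | 14 | 36.3% | 38.2% | 86.4% |

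All three exceed 85%, so the claim reproduces. (At n = 14 the unrounded limit is 54.0005%. Refusing x = 4 on that account would cut power to 69.8%, but that is a rounding artefact and not an error in the plan.)

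**Step 2. What 20% implies for survivors.** Let m be mortality and q the proportion of survivors with a non-fatal SAE. The any-SAE rate is m + (1 − m)q, so a 20% rate requires q = (0.20 − m)/(1 − m).

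- m = 15%: q = 0.05/0.85 = 5.9%, about 1 survivor in 17.
- m = 20%: q = 0.
- m = 25%: no solution, since deaths alone exceed 20%.

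In the other direction, with m = 20%, a 30% any-SAE rate needs a non-fatal SAE in 1 of 8 survivors (0.20 + 0.80 × 0.125 = 0.30). A 40% rate needs 1 of 4 (0.20 + 0.80 × 0.25 = 0.40).

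**Step 3. Power for the same bounds at other true rates.** The cut-offs c = 4, 8 and 14 stay fixed.

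| True any-SAE rate | n = 14 (54%) | n = 28 (46%) | n = 56 (37%) |
|---|---|---|---|
| 20% (as planned) | 87.0% | 91.0% | 86.4% |
| 25% (top of mortality range, no other SAE) | 74.2% | 75.0% | 57.1% |
| 30% (assumed) | 58.4% | 52.8% | 25.5% |
| 40% (assumed) | 27.9% | 14.9% | 1.4% |

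**Step 4. Bounds that could be excluded with at least 85% power.** For each rate, take the smallest c with P(X ≤ c) ≥ 0.85 and compute its upper limit.

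| True any-SAE rate | n = 14 | n = 28 | n = 56 |
|---|---|---|---|
| 20% | 54.0% (c = 4) | 45.7% (c = 8) | 36.3% (c = 14) |
| 25% | 61.0% (c = 5) | 49.4% (c = 9) | 42.0% (c = 17) |
| 30% | 67.5% (c = 6) | 56.5% (c = 11) | 47.5% (c = 20) |
| 40% | 79.4% (c = 8) | 66.7% (c = 14) | 58.2% (c = 26) |

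**The case against.** The power sentence is explicitly conditional and correct on its own input. The mortality range includes 20%, so with mortality near 15% and few non-fatal SAEs the assumption is possible. The mortality figure is a general one for CM, not a 14-day rate in this trial's selected population. The Sample size section speaks of an SAE background rate and of safety endpoints in the plural, so its use for any SAE is inferred from the primary endpoint. The article also condenses a fuller protocol, where the basis for 20% may be given. All of this stands. It makes the 20% an optimistic input rather than a miscalculation or a strict contradiction.

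A reader might infer more from the halting rules, where stopping probabilities were calculated for a true rate at which "the proportion of participants in a specific MedDRA classification group is a given percent (i.e., 25, 30, 40 or 50" percent. Those are scenario values for the operating characteristics of the rule. The section loosely speaks of expected rates, but the values are not estimates of background incidence and do not by themselves contradict 20%. Likewise, the example of 9 of 17 children with SAEs in different classes shows when the rule stays silent; it does not forecast a 53% rate.

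A reader might also infer that the trial will usually miss its bounds. The article does not support that. At 25%, the highest figure it gives for mortality, the bounds are still met more often than not at all three sample sizes. Rates of 30% and above are assumptions.

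Nor are these bounds the trial's only quantified safety property: the adult and pediatric halting rules also carry numbers. No escalation, halting or interim decision is tied to the bounds, and the sample size was set on feasibility.

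What the objection does not remove is that a stated figure for the primary safety endpoint uses a rate equal to mid-range mortality alone. The absence of a source can be left to the full protocol. The poor fit between the rate and the endpoint is visible in the article itself.

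**Conclusion.** The point holds as an optimistic planning input. The arithmetic is correct at 20%. That rate suits the any-SAE endpoint only if mortality is near the bottom of the article's range and non-fatal SAEs are uncommon, which sits badly with the high rates of adverse outcomes that the halting-rules section expects.

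The claim of over 85% power fails at all three sample sizes once the rate reaches 25%, with 74%, 75% and 57%. This takes no more than the top of the mortality range and no other SAE. It assumes that the quoted mortality applies within 14 days in this population. The falls at 30% (58%, 53%, 25%) and 40% (28%, 15%, 1.4%) depend on assumed rates and show sensitivity only. The consequence is an overstated precision for the safety conclusion, with no effect on how the trial is run.

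**What to change.** In the Sample size section, do one of the following:

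1. If 20% was meant as a death rate, say so and tie the three bounds explicitly to death. They then no longer describe the any-SAE primary endpoint.
2. Otherwise, replace 20% with a justified 14-day background rate of any SAE in CM, and restate the three bounds.
3. If no such rate is available, replace the single claim with the bounds excludable at 85% power or more over a range labelled as assumed. For n = 14, 28 and 56 these are 54/46/37% at 20% (as stated now), 61/49/42% at 25%, 68/57/48% at 30% and 79/67/58% at 40%.

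This is a text change. Under the second and third options the stated precision becomes less favourable wherever the rate is above 20%. The sample size, halting rules and conduct are unaffected.

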### Recruitment {15}

Healthy adults are recruited from the Ndirande township through community referrals to the research clinic. Adults with uncomplicated malaria are recruited from the Ndirande Health Center and surrounding health clinics.

Children with CM are recruited from the Accident and Emergency Department and inpatient hospital units of QECH in Blantyre and surrounding district referral hospitals. Adequate participant enrollment will be achieved by continuous screening for potential participants in all participating centers.

## Assignment of interventions: allocation

### Sequence generation {16a}

Pediatric participants are randomized in a 7:2 ratio for DON: placebo within each of cohorts 1 + 2, cohort 3, or cohort 4. Participants randomized to DON in cohort 4 may additionally be split into two different dose groups of DON. Computer-generated random numbers are used.

### Concealment mechanism {16b}

Assignment of pediatric participants to their randomization arm is performed by sequentially numbered opaque sealed envelopes prepared with the allocation sequence before the trial begins. The envelopes are stored in a secure location with access limited to key study personnel.

### Implementation {16c}

The allocation sequence is generated electronically and transcribed into opaque envelopes. After a caregiver provides consent for a pediatric patient to participate in the study, study personnel open the next unopened sequentially numbered envelope to reveal the group assignment and dosing calculation sheet.

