	Creatinine: ≤ 110 mmol/L / ≤ 1.2 mg/dL (males) or ≤ 90 mmol/L / ≤ 1.0 mg/dL (females)	Creatinine: ≤ 110 mmol/L / ≤ 1.2 mg/dL (males) or ≤ 90 mmol/L / ≤ 1.0 mg/dL (females)	No other explanation for coma by history or physical exam
		Glasgow coma score of 15	
		Respiratory rate ≤ 20 breaths/minute	
		Oxygen saturation ≥ 90% on room air	
**Exclusion criteria**	Pregnancy or lactation	Pregnancy or lactation	Pregnancy or lactation
	Allergy to ondansetron	Allergy to ondansetron	Allergy to ondansetron or ceftriaxone
	Currently taking highly active antiretroviral therapy (HAART)	Currently taking HAART	Currently taking HAART
	Currently taking anti-tuberculosis medications	Currently taking anti-tuberculosis medications	Currently taking anti-tuberculosis medications
	Participants attempting to become pregnant	Participants attempting to become pregnant	Cloudy cerebrospinal fluid (probable bacterial central nervous system infection)
			Malnutrition > 3 standard deviations below the mean weight for height and/ or mid-upper arm circumference ≤ 11.5 cm

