## Assignment of interventions: blinding

### Who will be blinded {17a}

Evaluators of safety and efficacy outcomes including study clinicians and nursing staff, as well as study participants and their parents/guardians, are blinded to the randomization assignment for pediatric participants.

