### Procedure for unblinding if needed {17b}

The study pharmacist maintains an unblinded version of the allocation sequence in a secure location for use in unblinding or for replacement should the original assigned envelope be damaged or lost. The pharmacist does not participate in other trial activities and will not share the list with study team members involved in participant follow-up activities. If circumstances arise where unblinding is needed before the end of the study (such as the occurrence of a suspected unexpected serious adverse reaction), the ISMs, who are physicians who are not investigators for this trial, will assess the child’s clinical status. Their report is shared with the sponsor and the DSMB. The DSMB then makes a recommendation for maintaining the blinding or unblinding which is communicated to the study sponsor.

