### Methods in analysis to adjust for protocol non-adherence and statistical methods to adjust for missing data {20c}

In both adult and pediatric studies, the primary population for analyses of all endpoints is all intent to treat (ITT) participants. Every effort will be made to minimize protocol deviations and minimize missing values. If there are deviations from protocol where treatment received differs from the treatment to which the participant is randomized, the primary analysis population will be “as-treated.” Because the primary goal is to determine dose safety, when dose randomized differs from dose received, we will analyze outcomes by the dose received and conduct sensitivity analyses on the ITT population with “as-randomized” assignment. To adjust for missing values in our analyses, we may use multiple imputation methods to measure dose effect while accounting for uncertainty arising from the missing value(s). We will generate 25 imputed datasets and fit the multivariate models accounting for model uncertainty as well as uncertainty from imputation.

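### As-treated analysis becomes primary for efficacy markers as well as safety, and the unmasked allocation envelope has no named opener and no fixed opening point

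*Protocol article*

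**What the plan says.** All places are in the Protocol article.

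**Analysis population, {20c}.** The default is that "the primary population for analyses of all endpoints is all intent to treat (ITT) participants". The exception follows at once: for deviations "where treatment received differs from the treatment to which the participant is randomized, the primary analysis population will be" as-treated. The reason given is that dose safety is the main goal. Outcomes are then analysed by dose received, and the as-randomised ITT analysis becomes a sensitivity analysis.

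**Allocation and blinding.**
- Implementation {16c}: once a caregiver has consented, "study personnel open the next unopened sequentially numbered envelope to reveal the group assignment and dosing calculation sheet". The envelope thus shows the group itself.
- Concealment mechanism {16b}: the envelopes can be reached by a restricted but unnamed set of staff.
- Who will be blinded {17a}: "Evaluators of safety and efficacy outcomes including study clinicians and nursing staff", as well as participants and their families.
- Procedure for unblinding {17b}: the pharmacist holds the unblinded list. "The pharmacist does not participate in other trial activities".
- Composition of the coordinating center {5d}: the study pharmacist is listed among those who run the trial day to day, alongside investigators and the study physician.

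**Eligibility and baseline.** Table 1 excludes children with cloudy CSF. Participant timeline {13} places the lumbar puncture at enrolment, and MRI (if available), TCD and at least 30 min of EEG before dosing.

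**Clocks, Exploratory endpoints.** The follow-up MRI is at 24 h from randomisation. The TCD is at 4 and 24 h from DON.

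**The concern.** The paediatric part is the only randomised, blinded part of the trial, and {20a} calls active dose against placebo the primary analysis. Three things in the text weaken that comparison or leave it loosely defined.

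First, analysis by dose received suits a safety endpoint. Extended to efficacy markers, it sorts children by what happened after randomisation, and the randomised comparison becomes secondary. The interim look at these markers informs the doses for cohort 4 ({21b}).

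Second, an envelope that shows the real group discloses it to whoever opens it. Study clinicians judge how SAEs relate to study product ({22}), and MRI, TCD and GOS-E depend on physician scoring ({20b}). If an opener also had one of those tasks, identical syringes would not protect the assessment.

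Third, if randomisation has no fixed place in the sequence, an endpoint timed from randomisation has no fixed post-dose time.

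**Working it through.** No stated figure is disputed. The arm totals reproduce: cohorts 1 to 3 give 4 + 10 + 14 = 28 DON and 2 + 2 + 4 = 8 placebo. Cohort 4 at 7:7:4 in 36 children gives 36 × 14/18 = 28 and 36 × 4/18 = 8. The total is 56 and 16, as in Sample size {14}.

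**1. Population rule.** Children who receive what they were randomised to are classified identically under both rules, so only mismatches matter.
- Wrong product given: under {20c} the child moves to the other arm in the primary analysis of every outcome. The safety reason supports this for SAEs. It gives no support for moving the child in the MRI, EEG or TCD comparison.
- No product given: treatment received differs from treatment randomised, so the exception applies, but there is no dose received by which to classify the child. The text names no arm.

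Leverage of one child on a rate: 1/14 = 7.1 points in a DON arm of 14; 1/8 = 12.5 points in the pooled placebo children of cohorts 1 to 3; 1/4 = 25 points in the 4 placebo children of cohorts 1 and 2 or of cohort 3. These describe small arms and do not measure bias.

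**2. Envelope.** The stated order constraints are:
- consent comes before study procedures ({26a}) and before the envelope ({16c});
- the envelope comes before dosing, because it carries the dosing sheet;
- lumbar puncture and baseline tests come before dosing ({13}).

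Nothing orders the envelope against the CSF result or the baseline tests. Opening before them and opening after them both satisfy every constraint. The adult timeline, by contrast, names both consent and confirmed eligibility before proceeding.

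On who opens it, {16c} says only study personnel, {17a} lists who is blinded, and no sentence says that the two sets do not overlap. The one role described as segregated, the pharmacist in {17b}, is not named as the opener and is placed in the day-to-day oversight group by {5d}.

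Illustration of what an unmasked envelope could disclose: assume fixed totals per cohort, all orderings equally likely, and a running tally known to the opener. With d DON and p placebo, the expected number of final assignments that are fully determined is d/(p + 1) + p/(d + 1).
- 4:2 gives 4/3 + 2/5 = 1.7.
- 10:2 gives 10/3 + 2/11 = 3.5.
- 14:4 gives 14/5 + 4/15 = 3.1.

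**3. MRI clock.** Let t be the time from randomisation to study product. The follow-up MRI then falls at 24 − t hours after product, and the late TCD at 24 hours, so the two differ by t. If the envelope is opened no later than premedication, t is at least 30 min. If it is opened before the EEG, and EEG and premedication run one after the other, t is at least 60 min. No upper end is stated, and t can differ between children.

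**The case against.** The strongest reply is that these are gaps in wording. Opening the envelope after consent is only a lower bound, and opening it after clear CSF and complete baseline tests fits every section. The blinding section does not blind all staff. Coordinators, a data manager and a pharmacist exist, syringes are identical, and a journal article usually leaves pharmacy procedures to the full protocol. Analysis by dose received is normal for safety, the exception applies only to mismatches, and a single directly observed dose should make wrong-product errors rare. The affected efficacy endpoints are exploratory, and the as-randomised analysis is kept as sensitivity.

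Much of this stands, and it rules out several stronger readings:
- A reader might infer that allocation is revealed before the CSF result and baseline tests, so that excluded children have already been randomised. The order is simply not stated.
- A reader might infer that blinding is broken, or that nobody independent is left to open envelopes. Neither follows, because an unblinded role could be assigned.
- A reader might take the 6 h limit in Eligibility criteria {10} as the size of the MRI timing error. That limit covers screening, not the interval from randomisation to dose.
- A reader might link the population rule to the envelope. The documents make no such link.

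The reply does not remove two points. The article itself states who opens the envelope, when and what it shows, and it does so too loosely for a double-blind design. It also states a population rule wider than its own reason.

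**Conclusion.** The point holds as three separate corrections, and it is a should-fix.

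1. The as-treated rule in {20c} goes beyond its safety rationale. It contradicts the opening statement that ITT is primary for all endpoints and leaves undosed children unclassified. This rests on the text alone.
2. The envelope procedure does not name an opener outside the blinded team and does not tie opening to eligibility or baseline tests. The statements about the pharmacist in {17b} and {5d} do not agree. A breach is possible, not shown. The predictability figures of 1.7, 3.5 and 3.1 hold only under the assumptions given with them.
3. The 24 h MRI and 24 h TCD run on different clocks. They differ by the interval from randomisation to product, whose size the documents do not give.

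How many children would be affected cannot be derived from the documents.

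**What to change.** - **{20c}:** Analyse safety in all dosed children by product received. Analyse the MRI, EEG and TCD markers as randomised, with dose received as the sensitivity analysis. State where a randomised but undosed child is counted.
- **{16c}:** Name an unblinded role outside care and assessment, such as the study pharmacist, to open the envelope and prepare the syringe. Allow this only once eligibility including CSF is confirmed and the baseline tests are recorded. Reconcile {17b} and {5d} with that role.
- **Exploratory endpoints:** Time the 24 h MRI from study product, as is done for TCD.

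The cost is protocol and procedure wording; the pharmacist already exists. There is one practical downside, because preparation would start only after the baseline tests. Intervention description {11a} has a 30 min thaw followed by reconstitution, shaking and drawing up, against a 30 min interval between premedication and infusion. Thaw plus reconstitution therefore takes somewhat longer than that interval, and the sequence in {11a} must be reconciled with the new opening point.
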